### 2.5. Sample Size

Our primary endpoint is the cumulative incidence of troponin elevation in the first three months of ICI treatment, compared to baseline levels. In order to obtain a sufficiently precise estimate of this incidence, the sample size was calculated based on the width of the 95% confidence interval.

As of January 2021, we added troponin to our standard-of-care blood analyses in ICI-treated patients. Approximately 10% of our patients had troponin elevation according to the definition in Section 2.4.1. Therefore, we assumed a 3-month cumulative incidence of 10% in our sample size calculation. To estimate this incidence with a precision of 7.5%, we need to include 249 patients. Precision is hereby defined as the width of the 95% confidence interval.

The dropout rate in the first three months is anticipated to be around 10%, mainly due to deaths. Therefore, death will be accounted for as a competing risk in the primary analysis. Simulations using Weibull distribution for time to death and time to troponin elevation showed that adding 10% in the calculated sample size still leads to a precision of less than 7.5% in the estimation of the cumulative incidence with death as a competing risk. Therefore, 276 patients will be included in the study.

### 2.6. Data Analysis

All patient data will be collected via REDCap (a Research Electronic Data Capture), a secure HIPAA (Health Information Portability and Accountability Act)-compliant Web-based application, using a standardized data collection form. Data needed for analyses will be extracted from REDCap [43,44]. For categorical variables, frequencies and percentages will be reported. Where values are missing, percentages will be calculated for the available cases, and the denominator will be mentioned. Continuous variables will be summarized as mean with standard deviation and range.

For the primary endpoint, the cumulative incidence of troponin elevation will be calculated with death as a competing risk. Cumulative incidences and corresponding 95% confidence intervals will be reported at 3, 6, 12, and 24 months and a cumulative incidence plot will be used to visualize the results.

Similarly, for the secondary endpoints elevation of NT-proBNP, CV abnormalities, and MACE, cumulative incidences and 95% confidence intervals will be calculated, considering death as a competing event.

Evolution of troponin, NT-proBNP, transthoracic echocardiographic, and electrocardiographic parameters over time will be first studied in a linear mixed effects model with a random intercept per subject to account for the correlation of measurements coming from the same individual. This model will be extended with patient and treatment characteristics and their interaction with time, to evaluate their impact on the evolution of these parameters.

The association between the longitudinal evolution of troponin levels and time-to-event endpoints (CV abnormality, MACE) will be studied in a joint model combining a linear mixed model for troponin and a sub-distributional proportional hazards model for the time-to-event taking into account death as a competing event for CV abnormality and MACE. Latent random variables and common covariates are used to link the sub-models for the longitudinal measurements with the competing risk failure time data. In this way, the association between the evolution of the longitudinal measurements and time to event can be evaluated. Furthermore, by modelling the time to event, the analysis of the longitudinal measurements is adjusted for non-ignorable missing data due to informative dropout caused by deaths.

Agreement between hs-TnT and hs-TnI (measured in all patients at baseline, 3, 6, 12, and 24 months) will be assessed in Bland–Altman curves and intraclass correlation coefficient (ICC) based on a two-way mixed effects model. The ICC and 95% confidence interval will be reported. Statistical analyses will be performed using R Software version 4.1.2 or higher.

As our clinical trial is an exploratory trial, secondary outcomes will be treated as exploratory results. Therefore, any definite finding for secondary outcomes will require further confirmatory studies to support possible findings. Hence, it is not needed to adjust for multiple testing for multiple secondary outcomes [45].

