Association between the evolution of troponin/NT-proBNP and CV abnormalities.Cumulative incidence of MACEs at 3, 6, 12, and 24 months. MACEs were defined as the composite outcomes of nonfatal stroke, nonfatal myocardial infarction, hospital admission for heart failure (HF), cardiac revascularization, and CV death.Overall survival *.Association between the evolution of troponin/NT-proBNP and MACEs.The difference in the evolution of hs-TnT/NT-proBNP/transthoracic echocardiography and electrocardiography parameters between combination therapy and monotherapy.Association between patient characteristics and troponin.Association between patient characteristics and NT-proBNP.Agreement between hs-TnT and hs-TnI levels at baseline, 3, 6, 12, and 24 months *.The proportion of severe immune-related non-CV toxicities (grades 3–5).Association between the evolution of troponin/NT-proBNP and severe immune-related non-CV toxicities (grade 3–5).Association between the evolution of troponin/NT-proBNP and overall survival.Association between the evolution of troponin and diastolic function (based on the recommendations of Nagueh et al. [42]).Association between the evolution of troponin and calcium score.

* These endpoints will also be evaluated in a preliminary analysis once 50 patients have reached their 3-month cardiac follow-up visit. The sample size was not adjusted for interim analysis as the release of preliminary results is not data-driven and does not affect the error structure of the trial. Study-level conclusions will only be made once the final results of the trial have been analyzed.

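### CV death is a component of MACE, yet the analysis section names death without qualification as the competing event for MACE; the two statements must be reconciled

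*Protocol article*

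**What the plan says.** Section 2.4.2 lists "Cumulative incidence of MACEs at 3, 6, 12, and 24 months" as a secondary endpoint and defines MACE as the "composite outcomes of nonfatal stroke, nonfatal myocardial infarction, hospital admission for heart failure (HF), cardiac revascularization, and CV death". CV death is therefore an event of interest. The stroke and myocardial infarction components are limited to nonfatal events.

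Section 2.6 sets the competing event for MACE twice:

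- Cumulative incidence, where the rule for the primary endpoint is carried over to the secondary ones: "elevation of NT-proBNP, CV abnormalities, and MACE, cumulative incidences and 95% confidence intervals will be calculated, considering death as a competing event".
- Joint model of troponin with a sub-distribution hazards model for time to event: "taking into account death as a competing event for CV abnormality and MACE".

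Neither sentence restricts death to non-CV death. No other part of the article does so, and none says that CV death takes priority as a MACE event.

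**The concern.** All-cause death is a proper competing event for troponin elevation, NT-proBNP elevation and the CV abnormalities of Table 1, because none of these contains a death component. MACE does contain one, so the shared rule contradicts the endpoint definition.

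If the analysis section is programmed as written:

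- A CV death with no earlier MACE component leaves the endpoint. A fatal infarction or stroke as first event then counts nowhere in MACE, since only the nonfatal forms are components. The same holds for a fatal myocarditis without an earlier component such as a heart-failure admission, because myocarditis is not itself a component.
- The MACE cumulative incidence at all four reporting times can only be lowered by this coding, never raised.
- In a sub-distribution model, patients with the competing event stay in the risk set as non-events. A patient who dies a CV death as first event would be handled as never having had a MACE, and the troponin–MACE association would describe a composite without CV death.

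**Working it through.** **1. The plan's own figures.** The article states a sample size for the primary endpoint only: "we assumed a 3-month cumulative incidence of 10% in our sample size calculation" and "To estimate this incidence with a precision of 7.5%, we need to include 249 patients", precision being the full width of the 95% confidence interval. With p = 0.10 and width 0.075:

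- Wald: n = (2 × 1.96)² × 0.10 × 0.90 / 0.075² = 245.9, so 246.
- Wilson interval: the smallest n with width at most 0.075 is 249, which reproduces the stated figure.
- Allowance for 10% dropout: 249 / 0.9 = 276.7 and 249 × 1.1 = 273.9, against 276 stated.

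The calculation rests on troponin elevation and not on MACE, so it is unaffected by this point.

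**2. The statements side by side.**

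| Endpoint | Contains a death component? | Competing event in Section 2.6 | Coherent? |
|---|---|---|---|
| Troponin elevation | No | Death | Yes |
| NT-proBNP elevation | No | Death | Yes |
| CV abnormalities (Table 1 plus pericardial effusion and new arrhythmias) | No | Death | Yes |
| MACE | Yes, CV death | Death | No |

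**3. Number of patients, simple count.** The article gives neither 24-month mortality nor the CV share of deaths for this cohort. Its only mortality figure for the cohort is indirect and early: "The dropout rate in the first three months is anticipated to be around 10%, mainly due to deaths". Assume 24-month mortality of 40–50% and a CV share of 5–10%:

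- Low: 276 × 0.40 × 0.05 = 5.5 CV deaths, which is 0.40 × 0.05 = 2.0 percentage points.
- High: 276 × 0.50 × 0.10 = 13.8 CV deaths, which is 0.50 × 0.10 = 5.0 percentage points.

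This counts every CV death. Those preceded by another MACE component are already events under either coding, so on these inputs the count is an upper limit.

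**4. Effect on the cumulative incidence, counting first events only.** Take constant hazards over 24 months (time unit 1):

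- CIF = λ₁ / (λ₁ + λ₂) × [1 − exp(−(λ₁ + λ₂))]
- λ_D = −ln(1 − all-cause mortality) and λ_M = −ln(1 − net risk of non-fatal MACE); s is the CV share of deaths.
- As written: λ₁ = λ_M, λ₂ = λ_D.
- As defined in Section 2.4.2: λ₁ = λ_M + s·λ_D, λ₂ = (1 − s)·λ_D.

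Example (all inputs assumed): mortality 40%, non-fatal MACE 5%, s = 5%. Then λ_D = 0.5108, λ_M = 0.0513, their sum is 0.5621 and 1 − exp(−0.5621) = 0.430.

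- As written: 0.0513 / 0.5621 × 0.430 = 3.9%.
- As defined: (0.0513 + 0.0255) / 0.5621 × 0.430 = 5.9%.
- Difference: about 2.0 points, or 5.4 of 276 patients.

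Over a wider assumed grid (mortality 30–60%, non-fatal MACE 3–10%, s 2–10%):

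| Mortality | Non-fatal MACE | CV share | As written | As defined | Ratio | Patients of 276 |
|---|---|---|---|---|---|---|
| 30% | 10% | 2% | 8.4% | 9.0% | 1.07 | 1.6 |
| 40% | 5% | 5% | 3.9% | 5.9% | 1.50 | 5.4 |
| 60% | 3% | 10% | 2.0% | 7.9% | 4.0 | 16.3 |

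The first and last rows give the extremes of the ratio. The model takes the CV-death hazard as unrelated to an earlier MACE. If an earlier MACE raises that hazard, fewer CV deaths are first events and the difference shrinks.

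**The case against.** The strongest defence is that the two sections can be read together. The endpoint definition governs, a competing event is by nature something other than the event of interest, and so death in Section 2.6 can be taken to mean death not already counted as MACE. The sentence is shorthand covering several endpoints, and detailed event coding usually belongs in a statistical analysis plan, which is not shown.

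That reading is plausible and may be what was meant. It appears nowhere in the text, however, and unqualified death is stated in two separate analyses. This is not a detail left for later: the article states the competing event, and states it in a form that conflicts with its own definition. What does belong in an analysis plan is the handling of deaths of undetermined cause, and its absence here is no finding.

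Some stronger inferences are tempting, and the document does not support them:

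- *That the trial intends to drop fatal CV events from MACE.* No such intention is declared. The loss follows only from literal coding.
- *That the 9.8% in the Introduction gives the CV share of deaths here.* It is a share of 82 treatment-related deaths (about 8) among 20,218 patients in a cited meta-analysis. It cannot be applied to all-cause deaths in this cohort.
- *That the lost events are those troponin predicts best.* The article does not say so. Its Discussion cites one cohort with no association between hs-TnT and overall survival, and another that links hs-TnI to MACE and all-cause mortality.

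The limits on importance also stand. Section 2.6 treats secondary outcomes as exploratory, and every death is still counted under overall survival.

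**Conclusion.** The contradiction holds. Its direction is known if the text is coded literally: MACE incidence is understated, and the troponin–MACE association refers to a different endpoint from the one defined. Its size cannot be derived from the article. The figure of about 6 to 14 of 276 patients (2 to 5 percentage points at 24 months) is an illustrative upper limit that rests on assumed mortality of 40–50% and an assumed CV share of 5–10%. Over the wider assumed grid, the incidence as defined is 1.07 to 4.0 times the incidence as written, a range that shows how little can be said about size. Severity is moderate: the endpoint is secondary and exploratory, and the primary endpoint and the 249/276 calculation do not change.

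**What to change.** In both places in Section 2.6, state that for MACE the competing event is non-CV death and that CV death counts as a MACE event. Keep all-cause death as the competing event for troponin elevation, NT-proBNP elevation and CV abnormalities. The rule for deaths of undetermined cause can go in the statistical analysis plan.

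The cost is one sentence in each of the two places and the matching event codes. No new data are needed, because the MACE definition already requires cause of death. The sample size stays as it is.

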#### 2.3.3. Transthoracic Echocardiogram (TTE)

A TTE will be performed in all patients at baseline, 3, 6, 12, and 24 months (Supplementary Table S1). A comprehensive evaluation of the systolic and diastolic function, ventricular and atrial geometry, will be performed following the guidelines by the American Society of Echocardiography on a Vivid E95 ultrasound system (GE Healthcare, Horten, Norway) [40]. Special attention will be given to acquiring a 3D measurement of the left ventricular ejection fraction (LVEF) and performing deformation imaging of the left ventricle global longitudinal strain (GLS). The right ventricular function will be evaluated by tricuspid annular plane systolic excursion (TAPSE) and peak systolic velocity S’ derived from color coded tissue Doppler imaging (TDI). Diastolic dysfunction will be based on an average E/e′ ratio > 15 and a LA area > 30 cm^2^.

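### The evolution models have a random intercept as their only random effect, so standard errors for time and characteristic-by-time terms are too small if patients' slopes differ

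*Protocol article*

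**What the plan says.** Section 2.6 (Data Analysis) of the protocol article names the initial model for evolution over time: "linear mixed effects model with a random intercept per subject to account for the correlation of measurements coming from the same individual". One model form serves troponin, NT-proBNP, echocardiographic and ECG parameters. The next sentence names the only extension: the model is "extended with patient and treatment characteristics and their interaction with time, to evaluate their impact on the evolution of these parameters". Those are fixed effects. No random slope and no serial correlation are mentioned.

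Section 2.4.2 (Secondary Endpoints) lists a contrast that this extended model would have to estimate: "The difference in the evolution of hs-TnT/NT-proBNP/transthoracic echocardiography and electrocardiography parameters between combination therapy and monotherapy".

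Section 2.6 then plans "a joint model combining a linear mixed model for troponin and a sub-distributional proportional hazards model" for CV abnormality and MACE, with latent random variables linking the two parts. It does not give the random effects of the longitudinal part.

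On timing, Section 2.3.3 says "A TTE will be performed in all patients at baseline, 3, 6, 12, and 24 months", while Section 2.3.5 has blood drawn at baseline and before every ICI cycle. The biomarkers can therefore have many more than five values per patient.

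On status, Section 2.6 says that "secondary outcomes will be treated as exploratory results", without multiplicity adjustment.

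**The concern.** A random intercept lets patients differ by a constant shift and nothing else. Given the fixed effects, all patients share one trajectory shape, and visits a few weeks apart are as strongly correlated as visits two years apart.

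The trial's own questions presuppose something different. Section 2.5 expects troponin elevation in about 10% of patients within three months and therefore not in the rest. Section 2.4.2 asks whether marker evolution is associated with CV abnormalities, MACEs, severe non-CV toxicity and survival. Those questions have content only if individual trajectories differ.

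When slopes do differ, a random-intercept model treats the variation as independent residual noise spread over all visits. Part of it is then averaged away as if each extra visit brought fresh information. Standard errors of time and covariate-by-time terms come out too small, and confidence intervals for the evolution contrasts too narrow. The problem grows with the number of samples per patient.

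**Working it through.** **The plan's own figure.** The documents give no figure for the evolution models. The only sample-size figures are 249 and 276, which concern the primary endpoint. For an incidence of 10% and a full 95% interval width of 7.5 points, the Wilson interval needs n = 249, as stated. Allowing for 10% dropout gives 249/0.9 = 276.7, against the stated 276. This point does not touch those figures.

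**Inputs.** From the documents: visits at 0, 3, 6, 12 and 24 months (Section 2.3.3), blood before each cycle (Section 2.3.5) and N = 276 (Section 2.5). Assumed, because the documents give no values: log scale, complete data, residual SD σe of 0.2 or 0.3, and between-patient slope SD σb of 0 to 0.5 per year.

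**Formula.** Let S be the sum of squared deviations of the m visit times from their mean. With a common schedule, the group-by-time estimate is the difference between the groups' mean within-patient slopes.

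- True variance of one patient's slope: σe²/S + σb².
- The random-intercept model puts the slope variation into its residual, which has expectation of about σe² + σb²·S/(m − 1). Its implied variance of one patient's slope is therefore σe²/S + σb²/(m − 1).
- Ratio of model SE to true SE: r = √[(σe²/S + σb²/(m − 1)) / (σe²/S + σb²)].
- Rejection rate of a nominal 5% test under the null: 2Φ(−1.96·r).

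If both groups have the same slope SD, the number of patients and the allocation cancel from r. A larger N does not cure the problem.

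**Five visits.** In years the times are 0, 0.25, 0.5, 1 and 2, with mean 0.75. S = 0.5625 + 0.25 + 0.0625 + 0.0625 + 1.5625 = 2.5, and m − 1 = 4.

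- σe = 0.2, σb = 0.1: r = √[(0.016 + 0.0025)/(0.016 + 0.01)] = √(0.0185/0.026) = 0.84.
- σe = 0.2, σb = 0.4: r = √[(0.016 + 0.04)/(0.016 + 0.16)] = √(0.056/0.176) = 0.56.
- σe = 0.3, σb = 0.2: r = √[(0.036 + 0.01)/(0.036 + 0.04)] = √(0.046/0.076) = 0.78.

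**24 monthly samples**, as a stand-in for per-cycle blood draws: S = 7.99 and m − 1 = 23. With σe = 0.3 and σb = 0.1, r = √[(0.01127 + 0.00043)/(0.01127 + 0.01)] = 0.74.

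**Formula and simulation side by side.** Each simulation used 276 patients and no true group-by-time difference. The σe = 0.2 runs had 20% of patients on combination therapy; the σe = 0.3 runs had two equal groups. There were 4,000 trials per five-visit setting and 2,000 per 24-sample setting.

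| Samples | σe | σb per year | r (formula) | Type I error (formula) | Type I error (simulated) |
|---|---|---|---|---|---|
| 5 | 0.3 | 0 | 1.00 | 5.0% | 5.0% |
| 5 | 0.3 | 0.1 | 0.92 | 7.3% | 6.9% |
| 5 | 0.3 | 0.2 | 0.78 | 12.7% | 12.4% |
| 5 | 0.3 | 0.3 | 0.68 | 18.2% | 18.1% |
| 5 | 0.3 | 0.5 | 0.59 | 25.0% | 24.8% |
| 5 | 0.2 | 0.1 | 0.84 | 9.8% | 9.4% |
| 5 | 0.2 | 0.2 | 0.68 | 18.2% | 18.4% |
| 5 | 0.2 | 0.4 | 0.56 | 26.9% | 27.9% |
| 24 | 0.3 | 0 | 1.00 | 5.0% | 5.0% |
| 24 | 0.3 | 0.1 | 0.74 | 14.6% | 15.6% |
| 24 | 0.3 | 0.2 | 0.50 | 32.4% | 31.8% |
| 24 | 0.3 | 0.3 | 0.39 | 44.8% | 44.6% |

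Allowing each patient a slope of their own brought the simulated error back to between 4.6% and 5.9% in the σe = 0.3 runs, and to about 5% in the σe = 0.2 runs.

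**The case against.** **The harm is conditional.** It needs slope variation or serial correlation, and the documents give no value for either. With slope SD zero the test holds its 5%. With residual SD 0.3 and slope SD 0.1 on five visits it reaches only about 7%. This stands, and it is why the size can only be given as a range.

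**The random-intercept model is a starting model.** The article says that evolution is first studied this way. This does not remove the point, because the extension it then names adds fixed effects only. The correlation structure is stated; it is not a detail left open for a later document.

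**The endpoints are exploratory.** This limits the consequence. The article uses that status to waive multiplicity adjustment, which does not make understated standard errors valid.

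**Two stronger readings are not supported.**

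- A reader might infer that hs-TnT and NT-proBNP are modelled untransformed. The article names no modelling scale. The sentence "Continuous variables will be summarized as mean with standard deviation and range" concerns descriptive summaries. Nor do the documents give a distribution for either marker. Skewness alone did not shrink standard errors either: raw-scale analysis of simulated log-normal data without slope variation gave 5.5% type I error and an SE ratio of 0.98.
- A reader might infer that the joint model can link events only to a patient's level. That follows only if the random-intercept structure is carried over, and the article does not say that it is.

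**Conclusion.** The point holds in a limited form. As written, the evolution model assumes equal correlation between all visits of a patient, and the named extension does not relax this. If patients' slopes differ, standard errors for time and characteristic-by-time terms are too small, including those for combination versus monotherapy.

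Under assumed slope SDs of 0.1 to 0.5 per year (log scale, residual SD 0.2 to 0.3, complete data), a nominal 5% test on five visits rejects in about 7% to 28% of null trials. With 24 samples and slope SD 0.1 to 0.3 the figure is about 16% to 45%. The direction is certain once slopes vary; the size in this trial is unknown.

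The primary cumulative incidence and the 276 patients are unaffected. This is an inexpensive improvement to secondary, exploratory analyses.

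**What to change.** In Section 2.6, replace the random intercept alone with a correlated random intercept and random slope for time. If that model does not converge, use a continuous-time AR(1) residual or cluster-robust standard errors, and name the fallback in advance. State the same random-effects structure for the longitudinal part of the joint model, so that its link to events can carry change as well as level.

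As a suggestion, and not as the correction of an error that the document shows, state the modelling scale for hs-TnT and NT-proBNP. A log scale would fit the primary endpoint's multiplicative rule of 1.5 times baseline (Section 2.4.1) and would let results be reported as ratios to baseline.

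The cost is analysis wording and some programming, wider intervals where slopes vary, and possible convergence problems. No visit, sample or patient is added.

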## 2. Methods and Analysis

### 2.1. Study Flow

The CAVACI trial, i.e., extensive CArdioVAscular characterization and follow-up of patients receiving immune checkpoint inhibitors, is a prospective, multicenter study. The study was approved by the central ethics committee of the Antwerp University Hospital (2021–1908, 2022–1908) and follows the standards of the Declaration of Helsinki and the ethical standards of the responsible committee on human experimentation. The study consists of routine investigations of biochemical parameters and a thorough CV follow-up at fixed time points. Patients included in the study will be followed for a total period of two years (Figure 1). Patients are currently being recruited via the multidisciplinary oncology board of each hospital. As of January 2022, 57 patients were enrolled.

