## 3. Discussion

Since 2020, CV follow-up has become a “hot topic” in ICI-treated patients. Shortly after our study was initiated, other research groups started publishing their results on similar CV screening programs in patients receiving ICIs.

To determine the role of GLS, global circumferential strain (GCS), and global radial strain (GRS) in ICI-treated patients, Quinaglia et al. conducted a retrospective study in which 75 patients with ICI myocarditis were compared with 50 ICI-treated patients without myocarditis [46]. They found that GLS, GCS, and GRS can predict CV events with better accuracy than LVEF, hs-TnT, and age, in patients who were diagnosed with ICI-induced myocarditis. However, only limited paired data were available for the analysis. Furthermore, pre-ICI TTEs were not investigated and TTEs during treatment were performed at different time points.

Kurzhals et al. retrospectively analyzed pre-treatment hs-TnT levels in 47 patients who subsequently received ICI therapy for locally advanced and/or metastatic melanoma [47]. One patient, who had normal pre-treatment hs-TnT, developed myocarditis. 28% of the patients had elevated levels at baseline, however, none developed ICI-induced myocarditis. There was no association between hs-TnT and overall survival. However, patients were only monitored for a short period of time.

Waissengein et al. performed a retrospective analysis in 135 patients treated with first-line pembrolizumab to evaluate whether baseline and longitudinal changes in hs-TnI could serve as a predictor for the development of MACEs and survival [48]. They found that abnormally elevated baseline hs-TnI levels (>50 ng/L) and levels prior to the second dose served as significant independent predictors for MACEs, with over an eightfold increase in relative risk. In addition, elevated baseline levels had a predictive role in all-cause mortality. However, troponin levels were only evaluated prior to the start and at cycle two. Echocardiography was only performed in 53 patients at baseline and 27 patients in follow-up. Therefore, the role of hs-TnI in the development of LV dysfunction could not be assessed. Moreover, some patients (27%) also received pembrolizumab in combination with other types of chemotherapy, which can also influence the effect on MACE and survival.

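### The joint model in section 2.6, as described, does not adjust the troponin trajectory for dropout due to death, and its coefficient mixes CV-event and death effects

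*Protocol article*

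**What the plan says.** Section 2.6 (Data Analysis) states the purpose: "The association between the longitudinal evolution of troponin levels and time-to-event endpoints (CV abnormality, MACE) will be studied in a joint model". The survival part is "a sub-distributional proportional hazards model for the time-to-event taking into account death as a competing event for CV abnormality and MACE". The connection is described as follows: "Latent random variables and common covariates are used to link the sub-models for the longitudinal measurements with the competing risk failure time data". The paragraph ends by claiming that, because time to event is modelled, "the analysis of the longitudinal measurements is adjusted for non-ignorable missing data due to informative dropout caused by deaths".

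Three other places matter:

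- Section 2.5 on early losses: "The dropout rate in the first three months is anticipated to be around 10%, mainly due to deaths".
- Section 2.1 on duration: "Patients included in the study will be followed for a total period of two years".
- Section 2.4.2, where the MACE composite ends with "hospital admission for heart failure (HF), cardiac revascularization, and CV death". For MACE, therefore, only non-CV death competes. For CV abnormality, every death does.

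**The concern.** A joint model corrects a longitudinal trajectory for dropout only if the process that causes the dropout shares the latent variables. Here the dropout process is death, while the process modelled is CV abnormality or MACE. On the sub-distribution scale a patient who dies without the event is carried forward as event-free, so the death itself tells the model nothing about that patient's troponin course. The property claimed does not follow from the model named.

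There is a second consequence. The sub-distribution coefficient describes cumulative incidence, which falls when the competing event becomes more frequent. If troponin is related to death, the coefficient combines that relation with the relation to the CV event.

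At stake are a trajectory that readers would take as death-adjusted when it is not, and an association estimate that is easily misread. Section 2.4 makes the association of the markers with CV abnormalities and MACEs part of the study objective.

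**Working it through.** **Figures in the plan.** The sample size reproduces and is not in question: a Wilson 95% interval at 10% first has width below 7.5% at n = 249, and 249/0.9 = 276.7 (249 × 1.1 = 273.9) against the stated 276. The article gives no 24-month mortality. If all of the 10% three-month dropout were deaths at a constant rate, mortality would be 1 − 0.9^8 = 57%. That is an extrapolation, so 20% to 60% is examined.

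**Check 1: is the trajectory corrected?** Simulation, 6 replicates of 4,000 patients. All inputs are assumptions: log-troponin with random intercept and slope, true mean slope 0.010 per month, slope SD 0.04, residual SD 0.3; death HR 2 per SD of the latent slope; cause-specific MACE HR 1 unless stated; baseline 24-month MACE 10%; measurements stop at death or event.

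| Scenario | Mixed model alone | Joint model as described | Joint model with linked death hazard |
|---|---|---|---|
| 40% mortality, 3-weekly sampling | 0.0048 | 0.0048 | 0.0100 |
| 60% mortality, 3-weekly sampling | 0.0018 | 0.0017 | 0.0102 |
| 40% mortality, visits at 0, 3, 6, 12, 24 months | 0.0023 | 0.0023 | 0.0103 |
| 40% mortality, 3-weekly, MACE HR 1.5 | 0.0043 | 0.0046 | 0.0100 |

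The described model performs essentially like no joint model. The optimiser gave numerical warnings, but the model with a linked death hazard recovered the true slope and a death HR of 1.94 to 2.01 against 2.0.

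**Check 2: what does the coefficient measure?** With constant cause-specific hazards c (event) and d (death) per year, the two-year cumulative incidence is

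CIF = c/(c + d) × [1 − exp(−2(c + d))],

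and the 24-month sub-distribution HR, high versus low troponin, is ln(1 − CIF_high)/ln(1 − CIF_low). Take c = −ln(0.90)/2 = 0.0527 and d = −ln(1 − m)/2 for baseline mortality m.

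Example with m = 40%, death HR 2, cause-specific HR 1: d = 0.2554 (low) and 0.5108 (high). CIF is 7.87% and 6.32%. The ratio is ln(0.9368)/ln(0.9213) = 0.80.

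| Cause-specific HR | Death HR | m = 20% | m = 40% | m = 60% |
|---|---|---|---|---|
| 1.0 | 2 | 0.90 | 0.80 | 0.70 |
| 1.0 | 3 | 0.81 | 0.65 | 0.52 |
| 1.2 | 2 | 1.08 | 0.95 | 0.84 |
| 1.5 | 2 | 1.34 | 1.19 | 1.04 |
| 1.5 | 3 | 1.21 | 0.97 | 0.77 |
| 2.0 | 2 | 1.78 | 1.58 | 1.38 |

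Every cell lies below its cause-specific HR. It falls below 1 when the cause-specific effect is weak, or when the death effect is strong and mortality high. In the fitted joint models with cause-specific HR 1, the estimate per SD of slope moved less: 0.95 (40%) and 0.86 (60%) with 3-weekly sampling, 1.01 and 0.93 with sparse visits.

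**The case against.** The best defence of the dropout claim is that the latent variables are linked to the competing-risk failure data, and death is one of those failure types. The full plan, which is not shown, may contain a death component. That is possible, and if so the correction could work. But the only survival sub-model the article names is the sub-distribution one for the CV event, and it credits the correction to modelling that event.

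Other points limit the concern, and they stand:

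- A reader might infer that troponin will look protective. The documents do not support that. The pembrolizumab cohort in the Discussion does report "In addition, elevated baseline levels had a predictive role in all-cause mortality", but the preceding sentence gives a more than eightfold relative risk of MACE. The melanoma cohort described there found no link between hs-TnT and survival. A null effect is least plausible for CV abnormality, because raised biomarkers alone meet the mild category in Table 1.
- A reader might infer that the model needs troponin values after death. That applies to a link through the current value. The article describes shared latent variables, which are fixed per patient.
- It would be too broad to say that death is not modelled at all, since CV death is within MACE.
- The 57% should not be read as expected mortality. Dropout is only mainly death, and no rate after three months is given.
- The sub-distribution HR is a legitimate description of cumulative incidence, which the plan also reports.
- Section 2.6 treats secondary outcomes as exploratory. That limits the consequences, but it does not make the adjustment claim true.

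**Conclusion.** The concern holds in this limited form. The statement that the troponin trajectory is adjusted for dropout due to death does not follow from the model described. If death depends on the latent troponin course, the trajectory stays about as biased as in the plain mixed model: in the simulations 0.0017 to 0.0048 against a true 0.010. The size rests on assumed inputs. If troponin evolution is unrelated to death, there is no such bias, but then no adjustment would be needed either.

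The sub-distribution coefficient is not a clean measure of association with the CV event. With a death HR of 2 and no cause-specific effect it is about 0.7 to 0.9. With a cause-specific HR of 1.5 or more it is usually attenuated and still above 1; the exceptions in the table need a death HR of 3 with mortality of 40% or more. A protective appearance is possible, not expected.

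The primary endpoint and the sample size are unaffected.

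**What to change.** In section 2.6, specify a joint model with two cause-specific hazards: one for the CV event and one for death without that event (non-CV death when the event is MACE). Link both to the troponin random effects with separate association parameters, and report both. The random effects should include a slope, since it is evolution that is to be linked. Keep the cumulative incidence, and the sub-distribution HR if wanted, as the description of absolute risk.

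If the sub-distribution model is kept alone, delete the claim of adjustment for dropout due to death. If the full plan already links a hazard for death, the text should say so.

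The cost is one extra association parameter, revised wording and some analysis time. No new data are needed. The linked death hazard would also inform the listed secondary endpoint on marker evolution and overall survival.
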